### Planned Statistical Analysis

All available daily body weights will be used for analyses. For aim 1, body weight and psychological and physiological parameters will be analyzed using a mixed effects model with time, food security status, baseline BMI, and age. Models will be checked for both normality and heterogeneity of variance in potential subgroups (eg, age and BMI category). Least squares means and tests for differences by food security group will be the primary results. The analysis of aim 2 will focus on correlations among the outcomes from aim 1. Both Spearman and Pearson correlation coefficients will be used to determine the pairwise relationships among outcomes. Depending on the collinearity among outcomes, factor analysis will also be used to explore these relationships. Analysis of the exploratory aim will determine whether the weekly patterns of change in body weight, food security status, and perceived stress are different by food security group and how well these measures are associated with each other over time.

For aim 1, mixed effects models will be used to model psychological and physiological parameters. Furthermore, a linear mixed effects model will be used to model the daily weight over time. In addition to overall changes in body weight between the groups adjusted for BMI, age, and other baseline covariates, smaller temporal changes (ie, weekly) will also be a focus. Modeling these smaller changes should account for the increased fluctuations in the weight of the food-insecure women.

For aim 2, mixed effects models will assess how daily weight change is associated with changes in psychological and physiological parameters. Initial weight, overall weight change, and weekly weight change will all be considered as predictors in addition to more exploratory weight variables, such as the number of days significantly above or below starting weight or average absolute daily weight changes. These variables will be interacted with food security status (group) to determine whether the weight changes have greater effect on food-insecure women.

Analysis of the exploratory aim will determine whether the weekly patterns of change in body weight, food security status, and perceived stress are different by food security group and how well these measures are associated with each other over time. The first part of this analysis will use a mixed effects model, testing food security group differences at each week, whereas the second part will test correlations. Mediation analyses will be applied using both structural mean models and principal stratification [89]. Weekly food assistance use may be used for subgroup analyses to explore how food assistance use influences body weight.

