### Aims

The RESPONSES study will address the following aims.

Aim 1: the study will longitudinally assess body weight in addition to psychological and physiological parameters in food-insecure and food-secure African American women with obesity. Body weight is collected to assess the change from week 0 to week 22. Psychological parameters (stress; executive function, decision-making, and motivation; and affect and nonhomeostatic eating) are measured via validated questionnaires. Physiological parameters are measured via 24-hour urine (cortisol) and blood (dehydroepiandrosterone-sulfate [DHEA-S], C-reactive protein [CRP], thyroid hormones, blood glucose, glycated hemoglobin, and insulin) samples as well as an allostatic load total score. These parameters are measured at week 0 and week 22 to examine changes in psychological and physiological mechanisms. We hypothesize that food-insecure African American women with obesity will demonstrate increased body weight and changes in psychological and physiological parameters consistent with elevated stress over 22 weeks compared with food-secure African American women with obesity.Aim 2: the study will examine associations between changes in body weight and psychological and physiological parameters in food-insecure and food-secure African American women with obesity. We are examining associations between (1) change in body weight collected over 22 weeks and change in psychological and physiological parameters collected 22 weeks apart and (2) changes in psychological and physiological parameters.Exploratory aim: the study will longitudinally examine cyclic patterns in body weight, food insecurity, and stress in food-insecure and food-secure African American women with obesity. Body weight is collected daily to assess average weekly change. Food insecurity and stress are assessed weekly via questionnaires. We are examining weekly patterns of body weight, food insecurity, and stress to determine how changes in body weight are related to episodes of food insecurity and stress. Finally, we are assessing mediation analysis of the psychological questionnaires.

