### Outcome Measures and Study Procedures

#### Overview

The primary outcome of the RESPONSES study is the change in *body weight*. The secondary outcomes include *psychological parameters* (stress; executive function, decision-making, and motivation; and affect and nonhomeostatic eating measured via psychological questionnaires) and *physiological parameters* (cortisol, DHEA-S, CRP, thyroid hormones [thyroid-stimulating hormone, free tri-iodothyronine, and free thyroxine], blood glucose, glycated hemoglobin, and insulin levels measured via blood and urine samples, as well as an allostatic load total score). Table 1 summarizes the data collection schedule of study procedures.

**Table 1 table1:** Schedule of RESPONSES (Effects of Episodic Food Insecurity on Psychological and Physiological Responses in African American Women With Obesity) study procedures.

Study procedure		Screening visit	Clinic visit 1 (week 0)	Remote visit 2 (week 11)	Clinic visit 3 (week 22)
Informed consent and HIPAA^a^ authorization		✓			
Health questionnaire and medical history		✓			
Medication inventory		✓			

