##### Allostatic Load

An *allostatic load total score* is calculated from selected clinic assessments described previously [55].

Textbox 2 presents each psychological and physiological parameter assessed in the RESPONSES study, as well as the relevant questionnaire or metabolic or endocrine assessment used to measure each parameter.

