### Sample Size and Statistical Power

Change in body weight was used to compute a minimum sample size for at least 80% power to examine response to episodic food insecurity longitudinally in African American women with obesity. Specifically, the power analysis is based on a study by Wilde and Peterman [23], which used nationally representative data to examine change in body weight over a 1-year period by food security status in women and men. We chose these data on body weight because we expect this measure to be responsive to episodic food insecurity. Wilde and Peterman [23] found that food-secure women had a 10.4% chance of gaining between 2.27 kg and 4.54 kg and a 20.7% chance of gaining >4.54 kg during a 1-year period. Food-insecure women had a 13% chance and a 31.7% chance of gaining between 2.27 kg and 4.54 kg and >4.54 kg, respectively. Using these estimates, an expected change over 22 weeks in the food-secure group is 0.54 kg, and an expected change in the food-insecure group is 0.80 kg. An SD of 22-week change in body weight, 0.24 kg [88], was increased to 0.30 kg to account for higher variability and ensure that the proposed study is well powered. Thus, with 60 participants, the study is well powered (>80%) to detect differences in body weight changes for aim 1. Furthermore, this study is also powered to detect a correlation as small as 0.40 for aim 2.

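### The Aim 2 pairwise correlations do not exclude two part-whole pairs: the allostatic load score with CRP and with HbA1c, both of which are components of that score

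*Protocol article*

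**What the plan says.** Under Planned Statistical Analysis, the article says "The analysis of aim 2 will focus on correlations among the outcomes from aim 1" and then "Both Spearman and Pearson correlation coefficients will be used to determine the pairwise relationships among outcomes". It adds: "Depending on the collinearity among outcomes, factor analysis will also be used to explore these relationships". No pair is excluded, and a score without an overlapping item is not mentioned.

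The Overview of Outcome Measures and Study Procedures gives the secondary physiological outcomes. They include "cortisol, DHEA-S, CRP, thyroid hormones" and "blood glucose, glycated hemoglobin, and insulin levels measured via blood and urine samples, as well as an allostatic load total score". CRP, HbA1c and the allostatic load score are therefore three separate outcomes.

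Textbox 2 gives the make-up of the score. There are five cardiovascular items (systolic and diastolic pressure, pulse, HDL, total cholesterol), three metabolic items (albumin, waist-to-hip ratio, HbA1c) and one immune item (CRP). The Allostatic Load section says only that the score "is calculated from selected clinic assessments described previously", with a citation. It does not show how items are scored or weighted.

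The Aims section describes Aim 2 in terms of changes: first, change in body weight against change in the other parameters, and second, "2) changes in psychological and physiological parameters". The sample size section says that "this study is also powered to detect a correlation as small as 0.40 for aim 2".

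**The concern.** A total correlates with each of its own items even when the items are unrelated to one another, because the item appears on both sides. If the allostatic load score is correlated with CRP or HbA1c, part of the coefficient is the marker correlated with itself. A test against zero then does not answer the question of interest, which is whether the marker is related to the rest of the physiological burden.

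The study wants to learn about mechanisms. A significant coefficient between allostatic load and inflammation or glycaemia could be read as a mechanistic link when much or all of it comes from how the score is assembled. If the total and its own components enter one factor analysis, the same shared content enters the correlation matrix being factored.

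**Working it through.** **Inputs from the article.** N=60; nine components, two of which (CRP, HbA1c) are also separate outcomes; detectable correlation 0.40.

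**Assumptions, not in the article.** Two-sided 5% tests. Equally weighted items, scored so that higher is worse. Either a sum of z-scores or a count of items in the highest-risk quarter. Test-retest correlation 0.5 to 0.9 over 22 weeks. Common inter-item correlation rho of 0 or 0.1.

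**1. The plan's own figure.** By Fisher's z, power = Φ(atanh(r)·√(n−3) − 1.96). For r=0.40 and n=60: 0.4236 × 7.550 − 1.96 = 1.24, so power is 89%. The smallest r with 80% power is tanh((1.96 + 0.84)/7.550) = 0.355, and r=0.40 needs n=47. The 0.40 statement is sound.

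**2. Score as a z-score sum.** For k items with common correlation rho, the item-total correlation is r = (1 + (k−1)·rho) / √(k + k(k−1)·rho).
- k=9, rho=0: r = 1/√9 = 0.33. Chance of significance at N=60: Φ(0.3466 × 7.550 − 1.96) = Φ(0.66) = 74%.
- k=9, rho=0.1: r = 1.8/√16.2 = 0.45.

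**3. Score as a high-risk count, levels at one visit.** Dichotomising an item at its upper quartile multiplies the independent-item value by φ(0.674)/√(0.25 × 0.75) = 0.734. So r = 0.734/3 = 0.245, and the chance of significance is 47%.

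**4. Score as a high-risk count, 22-week changes.** Simulated with 400,000 draws per setting. The last column is the correlation after removing the marker's own item from the score.

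| Retest | rho | r, full score | Chance of p<0.05, N=60 | r, item removed |
|---|---|---|---|---|
| 0.5 | 0 | 0.21 | 35% | 0.00 |
| 0.7 | 0 | 0.18 | 28% | 0.00 |
| 0.9 | 0 | 0.14 | 19% | 0.00 |
| 0.5 | 0.1 | 0.33 | 72% | 0.16 |
| 0.7 | 0.1 | 0.29 | 63% | 0.14 |
| 0.9 | 0.1 | 0.24 | 44% | 0.11 |

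With independent items the whole coefficient is artefact and disappears once the item is removed. With rho=0.1 some genuine association remains, and the leave-one-out score keeps it.

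**5. When would the overlap cancel?** For a z-score sum, the marker's covariance with the other eight items would have to equal minus its own variance. If those eight are mutually independent, that means a correlation of −1/√8 = −0.35 with their sum.

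**6. Reach.** There are ten physiological outcomes: cortisol, DHEA-S, CRP, three thyroid measures, glucose, HbA1c, insulin and allostatic load. They form 10 × 9/2 = 45 pairs, and two of these are part-whole pairs.

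**The case against.** The strongest reply concerns scope. The second limb of Aim 2 in the Aims section can be read as psychological against physiological changes only, and then neither pair arises. That reading is open. However, the statistical section is where the analysis set is stated, and it speaks of the Aim 1 outcomes without limiting the domain. The ambiguity should be settled rather than relied on.

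A second reply is that an article may leave such detail to the full protocol or analysis plan. That would answer a complaint about something missing. Here the article states an analysis set which, followed as written, contains two misleading pairs. The general mention of collinearity does not help, because its only consequence is a possible factor analysis, which does not remove shared content.

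Several stronger readings are tempting but unsupported:
- A reader might infer that these correlations will be presented as findings. Nothing in the article says how individual coefficients will be reported or interpreted.
- A reader might call the tests of zero correlation invalid. They do test whether the population correlation is zero; the difficulty is that zero is uninformative for a part-whole pair.
- A reader might say the correlations must be non-zero. A sufficiently negative relation with the other items would cancel the overlap.
- A reader might expect factor analysis to put the total, CRP and HbA1c on one factor. The analysis is conditional and exploratory, and with independent components CRP and HbA1c would be uncorrelated with each other. A shared factor is possible but not shown.
- A reader might set 0.33 beside 0.40 and doubt the power statement. The 0.40 is a detectable effect size, not a reporting threshold, and it is reproduced with margin.

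**Conclusion.** The point holds as a minor one. Under the literal analysis text, two correlations are biased upward by shared content. With nine equally weighted, independent items the expected value is about 0.33 for a z-score sum and about 0.14 to 0.21 for 22-week changes against a high-risk count. The corresponding chances of significance at N=60 are 74% and 19 to 35%, against a nominal 5%. These sizes depend on a scoring rule, item independence and retest correlations that the article does not give, so they show the plausible scale and do not predict the study's values.

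The reach is narrow: two of the 45 physiological pairs, and a smaller share once psychological outcomes are added. The primary outcome, the Aim 1 models, the body-weight correlations and the 0.40 power statement are untouched.

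**What to change.** Add a sentence to the Aim 2 analysis: when allostatic load is correlated with CRP or HbA1c, use the score recomputed without that component, or omit the pair. State also that the total will not be entered in a factor analysis together with its own components. It would help to say in the same place whether the second limb of Aim 2 covers all outcome pairs or only psychological against physiological ones.

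The cost is a sentence or two and a few lines of code. No new data are needed, and the full score remains usable against every outcome it does not contain.

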## Methods

### Overview of Study Design

This study is a 22-week longitudinal observation cohort study conducted at Pennington Biomedical Research Center in Baton Rouge, Louisiana. A total of 60 African American women with obesity—30 (50%) who report being food insecure and 30 (50%) who report being food secure at baseline—have been enrolled in the study. Daily body weights are remotely obtained from participants. Wearable devices are also given to participants to wear throughout the duration of the study to collect additional data. Weekly food security status and stress assessments are remotely conducted to ascertain episodes of food insecurity and self-reported stress. Psychological and physiological parameters are measured at the beginning (week 0 at clinic visit 1) and conclusion (week 22 at clinic visit 3) of the study. There is also a midpoint remote assessment of selected psychological parameters (week 11 at remote visit 2). Figure 1 presents the RESPONSES study design and timeline.

The study was registered at ClinicalTrials.gov (NCT05076487) on September 30, 2021.

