#### Remote Weekly Assessments

##### Food Security Status

This is assessed via a 2-item food insecurity screener [49,50], which references the previous week, to measure episodes of food insecurity. Weekly food assistance use (eg, SNAP and Special Supplemental Nutrition Program for Women, Infants, and Children benefits, as well as visits to food banks, food pantries, or soup kitchens) and receipt of income from any source (eg, traditional employment and federal financial assistance [Supplemental Security Income, Temporary Assistance for Needy Families, and unemployment benefits]) are also assessed to further augment the assessment of episodic food insecurity.

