##### Food Security Status

This is measured using a modified version of the 6-item Food Security Scale [56,57]. This scale is a well-validated measure of food security developed by researchers at the National Center for Health Statistics. Two or more affirmative answers indicate food insecurity.

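### The exploratory aim asks whether weekly patterns of food security status differ between cohorts formed on food security, but the test it names compares levels

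*Protocol article*

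**What the plan says.** Overview of Study Design fixes the cohorts by a one-time status: "30 (50%) who report being food insecure and 30 (50%) who report being food secure at baseline". For the visits, screening included, Questionnaires – Food Security Status says: "This is measured using a modified version of the 6-item Food Security Scale". It adds the cut-off: "Two or more affirmative answers indicate food insecurity".

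The weekly outcome comes from another instrument. Remote Weekly Assessments – Food Security Status describes a "2-item food insecurity screener [49,50], which references the previous week, to measure episodes of food insecurity".

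Planned Statistical Analysis then asks, for the exploratory aim, whether "weekly patterns of change in body weight, food security status, and perceived stress are different by food security group", and how strongly the measures go together over time. On method it says: "The first part of this analysis will use a mixed effects model, testing food security group differences at each week". The second part is to test correlations. No group-by-time term is named for this aim, although the same section does name interactions with food security group for aim 2. Nothing in the article notes that the cohorts are expected to differ in weekly food security status because of how they were formed.

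**The concern.** The question is about pattern over time: does weekly status move differently in the two cohorts? The named test asks something else: is the share of women reporting food insecurity different in week 1, in week 2, and so on? For body weight and perceived stress this is only a loose match between question and test. For food security status there is a further difficulty, because the outcome and the grouping variable measure the same construct. If women classed as food insecure at entry simply go on reporting food insecurity more often, at a constant rate, the weekly tests tend to be significant with no difference in pattern at all.

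What is at stake is interpretation. The study's stated contribution is the episodic nature of food insecurity, and the exploratory aim is where weekly patterns are examined. A run of significant weeks for this measure would not tell the reader whether food insecurity came and went, or only whether enrolment separated the women.

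**Working it through.** **The plan's own figure.** The article gives no power or error figure for this analysis. The one it does give, for change in body weight (Sample Size and Statistical Power), reproduces. The difference is 0.80 − 0.54 = 0.26 kg, the SD is 0.30 kg, and there are 30 per cohort. The standard error is 0.30 × √(2/30) = 0.0775, and 0.26/0.0775 = 3.36. Power is Φ(3.36 − 1.96) ≈ 0.92 (0.91 with the t distribution), consistent with the stated >80%. Two-sided alpha of 0.05 is assumed, since the article states none. This figure is not in dispute and has no bearing on the weekly food security test.

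**Inputs for the weekly test.** From the article: 30 women per cohort and 22 weeks. Assumed: weekly positive rates, flat in both cohorts, with 10% in the food-secure cohort; within-woman correlation 0.4; two-sided alpha 0.05.

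**One week, by formula.** With p̄ = (p₁ + p₀)/2, the chance that a weekly comparison is significant is

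Φ( [p₁ − p₀ − 1.96·√(2p̄(1 − p̄)/30)] / √([p₁(1 − p₁) + p₀(1 − p₀)]/30) ).

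Example, 40% v 10%: p̄ = 0.25, null standard error √(0.375/30) = 0.1118, alternative standard error √(0.33/30) = 0.1049. Then (0.30 − 0.2191)/0.1049 = 0.77, and Φ(0.77) = 0.78.

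**Twenty-two weeks, by simulation.** There were 2,000 runs per row, with flat rates and a woman-level random effect. The each-week comparison is a two-sample test in each week, standing in for the mixed-model contrast. The group-by-week contrast compares each woman's early and late weeks of a 4-week cycle between cohorts.

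| Food-insecure v food-secure rate | One week, formula | Share of weekly tests with p<0.05, simulation | Group-by-week contrast with p<0.05 |
|---|---|---|---|
| 10% v 10% | – | 5.6% | 5.6% |
| 20% v 10% | 19% | 20% | 4.3% |
| 30% v 10% | 49% | 49% | 5.2% |
| 40% v 10% | 78% | 80% | 5.2% |
| 50% v 10% | 94% | 95% | 5.8% |
| 60% v 10% | 99% | 99% | 5.3% |

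In every row the two cohorts have the same (flat) pattern. The each-week test follows the difference in level; the contrast keeps its nominal error.

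**The converse.** A strong 4-week cycle was also simulated in the food-insecure cohort, with women at different points of their cycle in any given study week. The each-week test was then significant in 50%, 80%, 95% and 99% of weeks at 30%, 40%, 50% and 60%, essentially the same as with flat data (49%, 80%, 95%, 99%). In that setting it does not respond to episodes at all. A term in study week would also miss cycles that are out of step with study week, because they average out. That is why calendar time matters in the fix.

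**The case against.** Several points on the other side stand.

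- **A reader might infer that the weekly test must come out positive. The documents do not support that.** Group is a one-time baseline status. The outcome is a previous-week status on a different 2-item instrument, in a study that expects status to change. With modest carry-over (20% v 10%) only about one weekly test in five is significant. Convergence of the cohorts would itself be informative.
- **A significant week is not a false positive.** If the true rates are 60% and 10%, rejecting equality is correct. The fault is that this answers a question about level, not the stated one about pattern.
- **A reader might infer that a level difference will be presented as evidence of cycling. No section says so.** The aim also relates changes in weight to episodes, and the second part of the analysis covers associations over time. Those correlations do not, however, test whether patterns differ by cohort.
- **Nor is the whole aim circular.** Body weight and perceived stress do not define the cohorts, and the question about patterns of change is sound for all three measures.

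One objection stands only in part. A mixed model that yields group differences at separate weeks normally contains group-by-week terms, and a condensed article may leave model detail to a fuller plan. But the article does name the test it will use, and that test is the each-week difference. Having the interaction in the model is not the same as basing the conclusion on it.

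**Conclusion.** The point holds as a mismatch between question and test for one measure. For weekly food security status, the named each-week group difference compares levels between cohorts selected on the same construct. It can be positive from enrolment alone when the weekly patterns are identical. How often depends on carry-over from baseline: from about 20% of weekly tests at 20% v 10% to 99% at 60% v 10%, against about 5% for a group-by-week contrast on the same data. These figures rest on assumed flat weekly rates, an assumed within-woman correlation of 0.4 and two-sided alpha of 0.05, none of which the article states.

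The importance is minor. It affects one of three measures in an aim labelled exploratory, and the primary outcome, change in body weight, does not depend on it.

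**What to change.** In the exploratory-aim paragraph of Planned Statistical Analysis:

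1. Keep the each-week between-cohort difference in food security status only as a check that the cohorts remained separated.
2. Base any claim that patterns differ on a group-by-time term in the mixed model (logistic for the binary screener), using all 60 women. Time may be study week or week of the month. The latter follows the monthly benefit cycle set out in the Background and can pick up calendar cycles that are out of step with study week.
3. Add, within the food-insecure cohort, a within-woman test of a time or week-of-month term.
4. Give week-to-week transition rates as description only. They do not by themselves show episodes: at a constant weekly probability of 0.4 with independent weeks, 2 × 0.4 × 0.6 = 48% of consecutive weeks differ. For the same reason, a random-intercept logistic model without a time term would not test for episodes.

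The cost is wording and a little more analysis, on weekly data already being collected. The downside is that an interaction test has less power than a comparison of levels, so a null result should be reported with its confidence interval.

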Research on the episodic nature of food insecurity, which is largely understudied in the literature (yet broadly hypothesized), may help elucidate its association with greater body weight (ie, obesity). Most studies that associate food insecurity and obesity are cross-sectional studies [24-28], which is a major limitation, given that food insecurity is considered a *cyclic phenomenon*, with episodes of food adequacy and food shortage [24,33,34]. Those who are food insecure may experience periods when food is more readily available and overconsume during this time, as well as periods of food scarcity that cause restricted food consumption [33,35,36]; for example, the largest federal nutrition assistance program, Supplemental Nutrition Assistance Program (SNAP), provides monthly benefits that are typically dispensed within the first 2 weeks of a month. Given this, food-insecure households may experience food availability in the first weeks of a month and overeat during this time, followed by food scarcity in the latter weeks of the month and constrained food consumption until the beginning of a new month [24,34,35]. Further evidence shows that soup kitchens see an increase in meals served toward the end of the month [37]. This highlights the need for longitudinal studies examining the episodic nature of food insecurity. Furthermore, alternating episodes of food adequacy and food shortage potentially shape body weight response in food-insecure individuals by increasing stress, which has both psychological and physiological manifestations [38].

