The significance of the RESPONSES study is evidenced by a number of factors, including (1) an explicit focus on health disparities driven by both sex and race or ethnicity as evidenced in African American women, who experience a greater prevalence of both food insecurity and obesity; (2) the assessment of episodic food insecurity via longitudinal observational data collection; and (3) the triangulation of body weight and psychological and physiological parameters in the context of episodic food insecurity as a stressor. These points of significance directly relate to the *Strategic Plan for NIH Nutrition Research* by addressing the multiple recommendations highlighted in the position paper on food insecurity and obesity by Brown et al [90]. This study explicitly acknowledges the *episodic nature* of food insecurity by using a longitudinal study design to examine how the cyclic nature of food insecurity relates to body weight. Furthermore, this study will investigate the mechanisms underlying the linkage between food insecurity and obesity by focusing on a range of relevant psychological and physiological factors. Examining the interplay between psychological and physiological factors may be important to understanding the disparate rates of obesity-related comorbidities (eg, diabetes and hypertension) in African American women. Finally, the results from the RESPONSES study will hold important considerations for the assessment of body weight and psychological and physiological parameters in studies, wherein the assessment of these markers might need to consider corresponding episodes of food insecurity.

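### The exploratory week-by-week group test runs on study week while the hypothesised cycle follows the calendar month, so with spread start dates this test averages most of the cycle away

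*Protocol article*

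**What the plan says.** The Background describes a monthly cycle. SNAP "provides monthly benefits that are typically dispensed within the first 2 weeks of a month", so food is available early, "followed by food scarcity in the latter weeks of the month and constrained food consumption until the beginning of a new month". The Aims section makes cyclic patterns in weight, food insecurity and stress the exploratory aim, and gives its purpose as relating weight change to episodes of food insecurity and stress.

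For that aim, Planned Statistical Analysis has two parts in one sentence: "The first part of this analysis will use a mixed effects model, testing food security group differences at each week", followed by correlations among the weekly measures.

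The only week numbering in the article runs from each woman's own first clinic visit (Overview of Study Design: parameters are "measured at the beginning (week 0 at clinic visit 1) and conclusion (week 22 at clinic visit 3"). Weekly assessments fall on a fixed weekday for each participant (Hunger and Fullness), not on a day of the month.

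Food assistance use and income receipt are recorded weekly; under Food Security Status in the weekly assessments, these "are also assessed to further augment the assessment of episodic food insecurity". The analysis text gives food assistance only an optional subgroup role and does not mention income receipt. It names no term for calendar month or time since benefit issue.

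**The concern.** If women start on different days of the month, a given study week is early-month for some and late-month for others. The group mean at that week then mixes full and lean phases, and peaks in some women offset troughs in others. The test can still show a group difference in level or in trend over 22 weeks. It cannot show the monthly rise and fall that motivates the aim. A flat result could be reported as absence of a cycle when the time axis had removed it.

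**Working it through.** **1. The plan's own figure.** No power is stated for the exploratory aim. The nearest figure is the power above 80% for aim 1 (Sample Size and Statistical Power): changes of 0.54 and 0.80 kg, SD 0.30 kg, 30 per group. Two-sided alpha 0.05 is my assumption.
- Standard error = 0.30 × √(2/30) = 0.0775 kg.
- (0.80 − 0.54)/0.0775 = 3.36; 3.36 − 1.96 = 1.40; Φ(1.40) = 0.919. The t version gives 0.910.

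The stated power reproduces, and it does not depend on cycle phase.

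**2. How much of a monthly cycle survives in a study-week mean.** Take a sinusoid of amplitude A and period P = 365.25/12 = 30.44 days, so 22 weeks hold 154/30.44 = 5.06 cycles. If start dates are uniform over w days, a large group's mean keeps the fraction |sin(πw/P)/(πw/P)|. The last column is the average for 30 women, by simulation.

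| Spread of starts | Formula | 30 women |
|---|---|---|
| 7 days | 0.915 | 0.918 |
| 14 days | 0.687 | 0.697 |
| 21 days | 0.382 | 0.408 |
| full month | 0 | 0.161 |

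For a full month the root-mean-square value is 0.182, matching 1/√30 = 0.183. So 16-18% survives and 82-84% is lost.

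**3. Power.** Simulation with 30 versus 30 women, 22 weekly means and 600 runs per setting. Assumptions not taken from the article: residual SD 0.6 kg, lag-1 autocorrelation 0.3, a sinusoidal cycle in food-insecure women only, benefit day uniform over days 1-14, and weekly food-insecurity reports that track the cycle. Starts are spread over a month.

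| Test | A = 0.15 kg | 0.25 kg | 0.40 kg |
|---|---|---|---|
| Group by study week (joint) | 0.05 | 0.03 | 0.05 |
| Sine/cosine of calendar month | 0.47 | 0.91 | 1.00 |
| Sine/cosine from own benefit date | 0.82 | 1.00 | 1.00 |
| Within-person weight-episode association | 0.74 | 0.99 | 1.00 |

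The first row equals alpha within simulation error: √(0.05 × 0.95/600) = 0.009.

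**4. Misalignment separated from choice of test.** If all women started on the same calendar day, the group-by-study-week test would have power 0.14 / 0.35 / 0.79, against 0.51 / 0.89 / 1.00 for the calendar-month harmonic. Misalignment therefore costs the step from 0.14 / 0.35 / 0.79 down to about 0.05. The rest of the gap arises because a joint test over 22 weeks is weaker than a two-term harmonic.

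**5. Week 11.** The midpoint is 77/30.44 = 2.53 months from baseline, about half a cycle out. With random start phase, the within-woman cycle shift over k months has SD √2 × A × |sin(πk)|. That is 1.41A at week 11 and 0.26A at week 22 (k = 5.0595 unrounded). Its sign depends on each woman's baseline phase, so with spread starts it averages to about zero in a group mean.

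**The case against.** A reader might infer that the exploratory aim as a whole must come out null. The documents do not support that. The second half of the same sentence plans correlations. Relating each woman's weight to her own reported episodes needs no common phase, and row four of the power table shows it can work. The article does not say the correlations will be within person, so this route is open but not secured. Planned Statistical Analysis also models weekly fluctuations for aim 1 and lists mean absolute daily weight change among the aim 2 predictors, which does not depend on phase.

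A reader might also infer that the midpoint results are biased ("There is also a midpoint remote assessment of selected psychological parameters (week 11 at remote visit 2"). Under the same spread-start assumption the half-cycle shift is individual noise, not a displacement of group means. Some instruments are little exposed: the distress scale covers 30 days and grit is a trait. Measures of the past week or the present moment carry more of it. A cycle covariate in every week 11 analysis is not warranted.

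Other objections stand in part. The article does not expressly define week as study week in this sentence; I infer it from the only index given. Start dates are not reported, and a narrow spread would leave most of the cycle intact. SNAP is offered as an example, and 16 of 28 food-insecure women with data work full time, so not every woman need follow one monthly cycle. Coding of a time variable is often left to an analysis plan. Here, though, the article names the unit of comparison, and that unit does not match its rationale. The Discussion's remark that "the assessment of these markers might need to consider corresponding episodes of food insecurity" concerns studies in general and adds little.

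**Conclusion.** The point holds for the first part of the exploratory analysis. Read on the article's week index, and with start dates spread over most of a month, the week-by-week group test retains about 16-18% of a monthly cycle's amplitude and has power near alpha at 0.15 to 0.40 kg. The spread is inferred from individual community recruitment between registration in September 2021 and data completion expected by the end of 2023. The power figures also rest on the assumed residual SD, autocorrelation and sinusoidal shape. The averaging-out itself depends on the spread of starts and on a roughly monthly period shared by the women. The primary aim 1 weight comparison is unaffected, so the change is worth making but does not threaten the main result.

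**What to change.** - In the exploratory mixed model keep study week as the trend term. Add cycle position as week of calendar month or sine/cosine of day of month, or as weeks since the last monthly benefit issue where that is recorded. Test group by cycle position as one joint test.
- Do not restart the clock at pantry or soup-kitchen visits or at any paycheck. The weekly form counts such visits as food assistance, while the Background reports that soup-kitchen meals rise late in the month. Mixing them with benefit issue would combine opposite phases.
- State that the correlations of weekly weight, food insecurity and stress are within person.
- Compare groups on each woman's detrended within-person weight SD, which needs no phase.
- For week 11, at most note that short-recall measures carry extra noise from cycle phase.

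The cost is revised wording and a little more analysis, with no new data. The cycle term assumes a roughly monthly period, and the SD comparison also picks up fluctuation that is not cyclic.
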